## Abstract

**Background:**

Rheumatoid arthritis (RA) and other rheumatic conditions not only fundamentally affect patients’ quality of life and physiological needs but are also negatively associated with work ability. The costs of poor work ability, which, in sum, are more than treatment costs, pose an economic burden to society and patients. Work ability in RA appears to be multifactorial; symptoms such as pain, swelling, and stiffness play a major role, as these directly affect functional disability. Also, RA patients typically suffer from reduced muscle strength. Lower extremity function and grip strengths especially impair their quality of life. However, the role of muscle strength and disease activity as determinants of work ability have not yet been studied.

**Objective:**

The primary objective of this study is to compare work ability in working-age participants with seropositive RA and with high and low disease activity; the secondary objective is to evaluate the association of muscle strength, functional ability, and frailty with work ability.

**Methods:**

This monocentric cross-sectional study will be conducted at a rheumatologic outpatient clinic and day hospital with approximately 100 seropositive RA patients aged <65 years. A clinical disease activity index as a measure for rheumatoid disease activity will be assessed during the patients’ routine visits at the clinic. Work ability, frailty, and functional disability will be evaluated with (self-reported) questionnaires as well as with physical tests (Work Ability Index/Score; Health Assessment Questionnaire Disability Index; Survey of Health, Ageing, and Retirement in Europe Frailty Instrument; Short Physical Performance Battery). Muscle strength will be determined with dynamometer measurements of isometric hand grip strength and quadriceps femoris muscle contraction strength. Sleep quality (Medical Outcomes Study Sleep Scale) and sexual functioning as physiological needs will additionally be determined with self-reported questionnaires.

**Results:**

For this study funding has already been awarded and enrollment has been completed. Data are currently being evaluated.

**Conclusions:**

This study will evaluate the association of work ability with modifiable parameters such as muscle strength and functional ability. It will provide further insights into work ability in RA and its associated risk factors. Any evidence of association will motivate further research, and the findings might encourage interventions focused specifically on improving muscle strength and lower extremity function to positively affect work ability.

**Trial Registration:**

ClinicalTrials.gov (NCT02581852); https://clinicaltrials.gov/ct2/show/NCT02581852 (Archived by WebCite at http://www.webcitation.org/6oNcelHtQ)

## Introduction

### Background

Rheumatoid arthritis (RA) is a chronic, systemic autoimmune disease that is most prevalent in individuals aged 40 years and above. RA affects about 1% of the world population, and the risk of developing RA is markedly higher in women. This disease is the most common form of chronic joint inflammation and causes joint pain, swelling, reduced muscle strength, and, as a consequence, impaired physical function [1]. In our experience, due to physical limitations, RA patients often suffer from impairment in their social life and their work life. Working is an important predictor of physical health–related quality of life in arthritis patients [2], and reduced muscle strength can cause physical limitations and a more frail condition, which in turn might have an impact on work ability. Beside obvious symptoms that directly cause physical limitations, physicians less often pay attention to physiological needs such as sleep and sexual functioning, which are also negatively associated with RA and in turn might unfavorably impact work ability.

### Rheumatoid Arthritis and Work Ability

Chronic diseases such as RA are negatively associated with work ability. Work ability, as described by Ilmarinen from the Finnish Institute of Occupational Health, is the interaction of individual determinants (health, competence, and attitudes) and the work environment [3]. It is determined by an individual’s perception of the demands at work and the ability to cope with them [4]. Although RA-induced work disability rates seem to decrease because of new therapeutic concepts, RA is still a fundamental burden for many patients [5]. The costs of work disability in rheumatic conditions are high, generally higher than the treatment costs [6]. Furthermore, from the patients’ perspective, work disability significantly affects their basic income [7].

Work disability in RA appears to be multifactorial; symptoms such as pain, swelling, and stiffness play a major role, as they directly affect functional disability [8]. RA is associated with loss of muscle mass and diminished strength. In healthy individuals, only a weak association between muscle strength and workability could be found [9]. The influence of strength on the work ability of RA patients has yet to be determined.

### Rheumatoid Arthritis and Muscle Strength

Body composition, particularly the amount of lean mass in the arms and legs, is associated with disability in RA patients. A large number of RA patients suffer from an increased loss of muscle mass with a significant impact on these patients’ quality of life [10]. This condition is commonly known as rheumatoid cachexia and has been reported in two-thirds of all RA patients, including patients with stable RA [11,12]. In geriatric patients, cachexia is associated with higher-than-normal concentrations of tumor necrosis factor-α (TNF-α), interleukin (IL)-1, and IL-6; a reduction in these proinflammatory cytokines is associated with weight gain [12,13]. The loss of body cell mass in RA patients is associated with proinflammatory cytokine–induced altered energy metabolism and intake despite a theoretically adequate diet [14,15].

In an x-ray computed tomography–based study, RA patients had a significantly higher body mass index and fat area but lower muscle area, muscle density, and muscle strength than healthy individuals. Furthermore, a higher degree of joint destruction and disease activity were shown to be associated with higher muscle deficits and impaired muscle strength [16]. Stucki et al [17] found that in patients with RA quadriceps muscle strength explained 12% of the variance in the self-reported activities of daily life, and women with RA were reported to have 20% lower quadriceps strength than the controls [18]. Isotonic and isometric hand exercise in RA patients can decrease pain and disease activity and increase muscle strength and function as well as quality of life [19]. Hand grip strength was shown to discriminate between various disease states of RA and seems to return to near-normative level when the disease is in remission [20].

### Rheumatoid Arthritis and Sleep

Most patients with RA experience insomnia, general fatigue, and mental fatigue, which negatively affect their physical and cognitive functioning and health. Arthritis pain can lead to sleep deprivation and a lack of sleep, which, in turn, contribute to increased pain and fatigue [21-24]. Poor sleep has also been shown to negatively influence work ability in otherwise healthy individuals [23].

### Rheumatoid Arthritis and Sexual Functioning

All aspects of life may be affected by RA. Pain, stiffness, and fatigue may impair not only functional disability but also sexual functioning in RA patients. As summarized by a recent review, aside from functional problems, depression, anxiety, a negative body image, reduced libido, and the application of certain drugs can negatively influence sexual activities [25].

### Rheumatoid Arthritis and Frailty

Frailty, as defined by Fried et al, refers to a state of increased vulnerability to external and internal stressors caused by a reduction in physiological reserves. It has been described as a clinical phenotype of unintentional weight loss, low energy, slow walking speed, low physical activity, and low grip strength (weakness). The presence of 3 out of 5 of these criteria indicates frailty, and the presence of 1 or 2 indicates a prefrailty state [26-28]. Frailty has been associated with a higher risk of adverse health outcomes, mortality, hospitalization, and functional impairment [26,29,30]. Several studies have shown a heightened inflammatory state in frail adults [31], and similar to other markers of frailty, gait speed has been shown to be associated with elevated levels of inflammation markers such as C-reactive protein (CRP), IL-6, and TNF-α [32].

The population of elderly and frail individuals with RA is increasing [24]. However, although older people are more likely to develop long-term illnesses, muscle loss, and reduced strength, age is not the sole predictor of frailty, and it may occur in younger patients [33]. Generally, RA patients appear to be more prone to frailty because loss of muscle mass and an increase in proinflammatory cytokines are clinical characteristics that are also present in young RA patients. The association of the frailty of young RA patients and work ability has yet to be examined.

### Aims and Objectives

The primary objective is to assess work ability in patients with seropositive RA in the working age and the association of work ability with disease activity (high, medium, low, or remission). The secondary objectives are to assess the association of muscle strength, lower extremity function, functional ability, and frailty with work ability in RA and determine the association of disease activity with selected physiological needs (sleep quality, sexual functioning) in RA.

## Methods

### Study Design

This study will be conducted as a monocentric cross-sectional study in seropositive RA patients at the rheumatology outpatient clinic and ambulatory day clinic of the Second Medical Division of the Sozialmedizinisches Zentrum (SMZ)-Süd, Vienna, Austria. Eligible patients will be consecutively included during an expected period of 1 year. Ethical review committee approval was obtained from Gemeinde-Wien (EK 15-173-0915). The study is registered at ClinicalTrials.gov [NCT02581852].

### Study Population

The study will involve 100 patients of working age between 18 and 65 years with seropositive RA according to 2010 European League Against Rheumatism classification. Eligible patients will be identified by staff members, and eligibility will be confirmed by the physician in charge at the outpatient or day clinic. Written informed consent will be obtained from each patient before enrollment. Patients who do not wish to sign the informed consent, are unable to follow advice for physical measurements and understand interview questions, and those with severe comorbidities will be excluded from the study. Questionnaires will be provided in German, English, Turkish, and Serbo-Croatian. Translations will be provided by Frauengesundheitszentren-Integration and Health Center (SMZ-Süd).

### Sample Size

The sample size was calculated to determine the difference in work ability between patients with high versus low disease activity. We estimate the percentage of patients with good work ability to be 40% in patients with high disease activity and 80% in patients with low disease activity. Furthermore, we estimate that 70% of the included participants will have a low disease activity. With an alpha risk of .05 and a beta risk of .2 accepted in a 2-sided test, 71 patients need to be included (results were obtained with nQuery Advisor 7.0, Statcon). With a 30% rate of loss assumed (because of noncompliance during physical tests, lack of understanding, or refusal to participate), a total of 100 included patients will be required.

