### Statistical Analysis

All statistical computations will be performed with SPSS version 22.0.2 (IBM Corp). The primary hypothesis of the study, “A difference in work ability and muscle strength exists in patients with high versus low disease activity,” will be tested with a Pearson chi-square test. For the descriptive statistics, mean values will be calculated for continuous variables, and categorical variables will be presented in percentages. Continuous parameters will be checked for normal distribution (Kolmogorov-Smirnov test, Levene test, histogram, and Q-Q plot check), and an unpaired Student *t* test will be performed, as appropriate. Otherwise, the Mann-Whitney U test will be used to identify differences between patients with high versus low disease activity. For categorical parameters, a Pearson chi-square test or Fisher exact test will be used if the cell count is <5. Binary logistic regression will be used to evaluate the impact of frailty, functional ability, and muscle strength on work ability. For metric data, Pearson correlation or Spearman rank correlation (given outliers or nonlinear but monotone associations) will be used to evaluate associations of interest. A *P* value of <.05 will be considered statistically significant for all tests.

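### The stated 71 patients do not follow from the stated inputs: 80% power needs about 51 to 64, depending on the test, so the printed beta and N do not belong together (the error is conservative)

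*Protocol article*

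**What the plan says.** The Sample Size section gives every input for a two-proportion comparison. Good work ability is put at "40% in patients with high disease activity and 80% in patients with low disease activity". For the group sizes, "we estimate that 70% of the included participants will have a low disease activity". The result follows: "With an alpha risk of .05 and a beta risk of .2 accepted in a 2-sided test, 71 patients need to be included". The software is named (nQuery Advisor 7.0), but not the test or any continuity correction entered into it. The section then allows for attrition ("With a 30% rate of loss assumed") and concludes that "a total of 100 included patients will be required".

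The Statistical Analysis section says that the primary hypothesis, high versus low disease activity, "will be tested with a Pearson chi-square test". For categorical parameters it also allows Fisher's exact test where a cell count is below 5.

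**The concern.** The section prints both the inputs and the answer, so the calculation can be repeated without a fuller document. When it is repeated, 71 is well above what 80% power requires. Either the stated beta, the test behind the calculation or the meaning of 71 is not as written.

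What is at stake is how the result is read. A reader facing a non-significant comparison will take the design to have had 80% power at 71 evaluable patients. On the stated assumptions that is not the power the design had. The paragraph is also the only basis given for enrolling 100 patients.

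**Working it through.** **Inputs (Sample Size section).** p_high = 0.40; p_low = 0.80; difference d = 0.40; two-sided alpha 0.05 (z = 1.960); power 0.80 (z = 0.842); 70% low activity. The share with high activity is not stated. Taking all of the remaining 30% as high is an assumption; it gives a low:high ratio k = 7/3.

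**Uncorrected Pearson test (the planned primary test).** Pooled proportion: 0.3 × 0.40 + 0.7 × 0.80 = 0.68.

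n_high = [1.960 × √(0.68 × 0.32 × (1 + 3/7)) + 0.842 × √(0.40 × 0.60 + 0.80 × 0.20 × 3/7)]² / 0.40²
= [1.960 × 0.5575 + 0.842 × 0.5555]² / 0.16 = 15.22

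Total = 15.22 × 10/3 = 50.7, so 51 (15 + 36). It is 54 if the high group is rounded up to 16 and the 7:3 ratio is then kept.

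**Continuity-corrected.** n' = (15.22/4) × [1 + √(1 + 2 × (1 + 3/7)/(15.22 × 0.40))]² = 18.62. Total = 18.62 × 10/3 = 62.05, so 63 (19 + 44), or 64 if the ratio is kept after rounding.

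**Fisher's exact test.** By enumeration of the two binomial distributions, power passes 80% at about 57 patients (17 + 40; 80.4%). If the two-sided p-value is defined by doubling the one-sided one, power is 77.9% at 60 (18 + 42) and 80.5% at 64 (19 + 45).

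**Attempts to reach 71 with the stated alpha, sidedness and power.**

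| Variant | Total N |
|---|---|
| Pearson, uncorrected | 51 (54) |
| Unpooled variance | 51 |
| Arcsine | 53 |
| Log odds ratio | 56 |
| Fisher's exact | about 57; 64 with the doubled p-value |
| Continuity-corrected | 63 to 64 |
| Split reversed (70% high) | 55; 66 corrected |
| 1:1 split | 46; 56 corrected |

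None comes within two patients of 71.

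**Exact power at the stated 71 (21 + 50).** Pearson 92.4%, Fisher 87.8%, continuity-corrected 85.8%. The expected cells on the stated rates are 21 × 0.4 = 8.4, 21 × 0.6 = 12.6, 50 × 0.8 = 40 and 50 × 0.2 = 10. All exceed 5, so Pearson rather than Fisher is the test to expect.

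**Loss step.** 71/0.7 = 101.4 and 100 × 0.7 = 70. At 70 evaluable patients (21 + 49), exact Pearson power is 90.5%.

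**Sensitivity to the assumed split.** The Data Collection and Procedures section defines four CDAI categories, and no share is given for moderate activity. As an illustration, with 50 low-activity patients the normal-approximation power of the uncorrected test is 80% with 13 high-activity patients and 73% with 10.

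**The case against.** The strongest reply is that the discrepancy is harmless: on the stated inputs 71 patients give more power than claimed, and enrolment is complete. That stands as far as it goes. A reader might infer that the study is underpowered or its inference endangered; the stated figures show the opposite. What remains is that the printed design figures contradict one another.

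A second reply is that the sizing test is not named, so 51 need not be the benchmark. This also stands. The excess is 20 patients (71 − 51, or 39%) against the planned Pearson test, but only 7 to 8 (11% to 13%) against the continuity-corrected figure. The size of the gap depends on the test; its existence does not.

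Two further inferences are tempting and unsupported.

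- That 100 is a separate error because 71/0.7 rounds up to 102. The difference is one or two patients, the abstract describes the target as approximate, and 70 evaluable patients retain about 90% power. This is rounding.
- That 71 already contains the 30% loss, or came from 90% power. Nothing in the article says so. Dividing the required 51 by 0.7 gives 72.9, so 73. The uncorrected formula at 90% power gives 67.85, so 68, or 70 if the ratio is kept after rounding. Several routes land near 71, and the article does not distinguish between them.

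**Conclusion.** The point holds in a limited form. The figure of 71 is wrong as written for the stated rates, split, alpha and beta: 80% power needs about 51 (Pearson), 57 (Fisher) or 63 to 64 (continuity-corrected) patients, and 71 gives about 92%, 88% or 86%. The error is conservative on the stated assumptions.

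These figures rest on the assumed 40% and 80% rates and on all non-low participants having high activity. The second assumption is not in the article. If part of the 30% has moderate activity and is left out of the contrast, the high group shrinks and the apparent margin can disappear. The article gives no share from which to say how far.

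**What to change.** Rerun the calculation and restate the paragraph, naming the test, any continuity correction, the power and the assumed high:low split, so that N follows from them. For example: with a 30:70 high:low split, about 51 evaluable patients give 80% power with the uncorrected Pearson test, and the roughly 70 evaluable patients expected from 100 enrolled with 30% loss give about 90%. If 71 came from another power or test, correct the stated beta or name that test instead. Add that power is lower if some of the non-low 30% have moderate activity.

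The cost is one rerun and one paragraph. Enrolment does not change, and since the article reports that the data are still being evaluated, the correction can precede the reading of the results.

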### Strengths and Limitations

The study is limited by its cross-sectional design, which allows us to draw a conclusion about association but not causality. However, as we intend to analyze multiple outcomes and potential risk factors, we considered this approach to be ideal for generating hypotheses for further interventional approaches or longitudinal studies. Another potential limitation might be the pain-related noncompliance of patients during physical measurements. High disease activity and pain may possibly lead to some degree of bias in the results.

An advantage of this study is the availability of patients from various settings. Through recruitment at an outpatient clinic and a day clinic, the whole spectrum of different disease activities can be investigated. All study-related measures can be performed in short time periods without the necessity of a second appointment, thereby assuring high patient compliance and a marginally low drop-out rate.

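### The 30% loss allowance deducts non-participants from 100 included patients, and separately the stated 80% power does not match 71 or 100 patients

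*Protocol article*

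**What the plan says.** All references are to the protocol article.

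- **Sample Size, effect and split.** Good work ability is put at "40% in patients with high disease activity and 80% in patients with low disease activity", and it is assumed that "70% of the included participants will have a low disease activity".
- **Sample Size, base number.** "With an alpha risk of .05 and a beta risk of .2 accepted in a 2-sided test, 71 patients need to be included".
- **Sample Size, inflation.** An allowance of 30% for loss is then made, on account of noncompliance in the physical tests, "lack of understanding, or refusal to participate), a total of 100 included patients will be required". The 30% is not divided among its three reasons.
- **Study Population.** The study is to involve 100 patients, and written consent comes before enrollment. Those excluded include "Patients who do not wish to sign the informed consent, are unable to follow advice for physical measurements and understand interview questions".
- **Strengths and Limitations.** Everything is measured without a second appointment, "thereby assuring high patient compliance and a marginally low drop-out rate". The same section also names pain-related noncompliance during the physical measurements as a possible limitation.
- **Primary Outcome and Statistical Analysis.** Work ability is self-reported by questionnaire. The primary hypothesis, high versus low disease activity, is tested with a Pearson chi-square test.

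**The concern.** There are two separate problems.

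**What the 30% counts.** Someone who declines consent is never an included patient, so cannot be subtracted from 100 included. Someone who cannot understand the questions is excluded under the eligibility rules. Only the remaining reason, noncompliance during physical tests, plainly arises after inclusion. A 30% loss among included patients is also hard to square with a marginally low drop-out.

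The distinction matters for reporting. Non-participants bear on how representative the sample is. Losses after inclusion bear on bias, and the article itself links noncompliance to high disease activity and pain, which is the exposure being compared. One pooled loss rate blurs the two.

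**What power the numbers give.** The paragraph attaches 80% power to 71 patients. If that pairing is wrong, the stated design property is wrong whatever is decided about losses.

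**Working it through.** **Inputs (Sample Size; test from Statistical Analysis).** p1 = 0.40 (high activity), p2 = 0.80 (low activity), difference d = 0.40, split 30:70 so k = 7/3, two-sided alpha .05 (z = 1.960), power 80% (z = 0.842).

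**1. The step from 71 to 100.** 71 / (1 − 0.30) = 101.4, which rounds up to 102. Conversely, 100 × 0.70 = 70. The stated 100 therefore agrees with a 30% loss to within two patients, so the arithmetic of this step is not the problem.

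**2. The base number of 71.** With the usual pooled-variance formula:

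n1 = [z_α √((1 + 1/k) p̄(1 − p̄)) + z_β √(p1(1 − p1) + p2(1 − p2)/k)]² / d²

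- p̄ = 0.3 × 0.40 + 0.7 × 0.80 = 0.68, so p̄(1 − p̄) = 0.2176.
- First term: 1.960 × √(1.4286 × 0.2176) = 1.960 × 0.5575 = 1.093.
- Second term: 0.842 × √(0.24 + 0.16 × 3/7) = 0.842 × 0.5555 = 0.468.
- n1 = (1.093 + 0.468)² / 0.16 ≈ 15.2, so 16 high and 38 low, **54 in total**.
- With continuity correction: n1 = (15.2/4) × [1 + √(1 + 2(k + 1)/(15.2 k d))]² ≈ 18.6, so 19 and 45, **64 in total**.

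Other conventions do not give 71 at 80% power either: arcsine about 53, unpooled variance about 51, equal groups 46 (56 with correction), reversed split about 57 (67 with correction). A total of 70 (21 and 49) is what the uncorrected formula gives for 90% power.

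**3. Power for a given number analysed.** Pooled formula: z_β = (d√n1 − 1.093) / 0.5555, with n1 = 0.3N. At N = 70: (0.4 × √21 − 1.093) / 0.5555 = 1.33, power 90.9%. The exact column enumerates both binomials with the uncorrected Pearson test.

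| Analysed | Groups (exact) | Pooled formula | Exact Pearson |
|---|---|---|---|
| 70 | 21 / 49 | 90.9% | 90.5% |
| 71 | 21 / 50 | 91.2% | 92.4% |
| 80 | 24 / 56 | 94.1% | 94.4% |
| 90 | 27 / 63 | 96.2% | 96.0% |
| 100 | 30 / 70 | 97.6% | 97.4% |

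The rows for 80 and 90 correspond to two thirds and one third of the 30% being lost after inclusion. Those shares are assumptions, because the article gives none.

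**4. Dependence on the two-group split.** The table places every analysed patient in the high or low group. Aims and Objectives and the disease activity definitions list four categories, including moderate and remission. If half of 100 fell outside the two compared groups (an assumption), 15 versus 35 would remain and exact Pearson power would be 79.3%.

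**5. Which losses reach the primary comparison.** Work ability comes from a questionnaire and disease activity from the CDAI (joint counts and global ratings). Neither uses the dynamometer or the lower-extremity tests. A patient who cannot complete a strength test can still be counted in the primary comparison unless deliberately dropped from it.

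**The case against.** - **The step to 100 is consistent with 30%.** This stands. A reader might infer that the loss wording is what separates 100 from 80% power. It is not: with the full 30% accepted, 70 analysed already give about 91%. The power mismatch comes from the base of 71 and would remain if the loss reasons were perfectly worded.
- **Part of the allowance is legitimate.** This stands. Noncompliance during physical tests occurs after inclusion and the article expects some. Only consent is explicitly placed before enrollment; no timing is given for excluding those who cannot understand, so poor understanding might emerge after consent. It would be too strong to say that none of the 30% can fall among included patients.
- **A cautious allowance can sit beside an optimistic expectation.** This stands in part. The low drop-out claim is argued from the single appointment and carries no figure, so it does not fix how many of 100 will be analysed. The two statements still need reconciling.
- **Nothing says that 100 were approached.** True. The abstract, Study Population and Sample Size all describe 100 patients in the study. That approximately 70 were included is only one way to make sense of refusal as a loss reason.
- **No harm follows.** On the stated inputs power is higher than claimed, the target difference is explicit, and enrollment is complete. This limits the weight of the point. It does not make the stated loss basis or power correct.

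**Conclusion.** The point holds in two limited parts.

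First, the loss basis contradicts the eligibility rules. Refusers cannot be lost from 100 included patients. What can be lost is noncompliance during tests and any poor understanding found after consent, and this need not remove a patient from the primary comparison.

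Second, a beta of .2 fits none of the sizes given. The stated inputs need about 54 patients, or about 64 with continuity correction. Power is about 91-92% at 70 to 71 analysed and about 97% at 100.

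The power figures assume 40% versus 80%, a 30:70 split, and all analysed patients in the two compared groups. A reader might conclude that the study is underpowered, or that it certainly has 96-97% power. The documents support neither. On their own inputs power exceeds 80%, but how much depends on how many patients enter the high-versus-low comparison, which is not stated. This is an inconsistent justification of the sample size, not a demonstrated shortfall.

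**What to change.** Revise the Sample Size paragraph and align Study Population and Strengths and Limitations with it:

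1. Say whether 100 is the number approached or the number included.
2. Limit the loss allowance to losses after inclusion, and report refusal and ineligibility separately as non-participation.
3. State how many patients are expected in the high-versus-low comparison, and whether moderate-activity and remission patients enter it and in which group.
4. Correct the pairing of 71 patients with 80% power, and restate power for the number in item 3: about 91% at 70, 94% at 80, 96% at 90, 97% at 100. Give the condition that all of them fall in the two groups at 30:70, and recompute if the groups are smaller.

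The cost is the rewording of one paragraph and small matching edits. No patients and no new analysis are needed. As enrollment is complete, the final report can give the actual numbers approached, included and analysed.
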